### Ethical considerations

The population served by the SMRU clinics are predominantly migrant workers and refugees. These individuals have lower levels of income and education, poorer health outcomes, and migratory housing arrangements. SMRU has been serving this population for over 30 years and has experience of working with vulnerable populations. SMRU medics, nurses and health workers are recruited from the same areas as the patient population and are sensitive to their needs. All communication is conducted in the preferred language of the patient. We ensure that participation is voluntary and that it is clearly understood that participation in the study can be ceased at any time without effect to the care provided.

Trained counsellors will seek the mother’s consent after the patient information sheet has been discussed. All queries from the mothers will be answered and those who agree will sign the consent form. Trained personnel carry out all capillary and venous blood taking to reduce infant’s discomfort from these procedures. All data collected will be treated confidentially and stored securely.

### Data collection and analysis

Data will be collected on pre-coded forms and stored in a purpose-designed Microsoft Access database. A hypothesised causal diagram for how factors associated with NH may be connected will be constructed. The incidence of NH and corresponding 95% confidence interval will be calculated within the population of newborns born in the SMRU clinics only; eligible newborns born outside SMRU facilities will be excluded from the incidence analysis as they might falsely increase the incidence of NH in this population. Following this, univariate and multivariate logistic regressions will be performed to identify risk factors for NH. Stepwise logistic regression modelling with backward elimination will be performed on the subset of candidate risk factors selected based on *p*-value < 0.10 in the univariate regression analyses. Key confounders, identified a priori in the causal diagram will be forced into the model. To estimate the association between NH and neurocognitive score, multivariate linear regression will be performed with adjustment for the confounders identified in the causal diagram. Pre-planned subgroup analysis will be conducted in order to identify risk factors associated with moderate and severe NH and estimate the association between NH and neurodevelopment (measured as a continuous neurocognitive score). The description of the clinical course will be supported by SBR measurement tracking recorded on the treatment graph. SBR measurements will be modelled to understand factors impacting on trends [6]. A senior biostatistician will oversee the statistical analyses.

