### Outcomes

The primary outcome of this study will be to measure the relative risk of factors associated with moderate and severe NH in infants born at SMRU and to calculate their population-attributable fraction. The secondary outcomes will be to: i) determine the incidence of NH and of prolonged jaundice; ii) measure the changes in the trend of consecutive SBR and the duration of phototherapy according to the risk factors; iiia) compare the clinical condition (anaemia incidence, stunting prevalence) between severe and moderate NH, and normal bilirubinaemia in the first year of life; iiib) compare the neurocognitive developmental, tone and behaviour total scores at one year of life between severe and moderate NH, and normal bilirubinaemia.

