### Sample size

A convenience sample including all births within a one year timeframe at each site was chosen. Based on previous SMRU studies, it is assumed that most mothers will agree to participate in this study and that 15% of infants will be lost to follow-up before completion of the study. More than 90% of women in the area attend ANC. In 2014 more than 80% of women who attended ANC care birthed at SMRU clinics (2040 infants born alive of 28 weeks or more gestational age). It is expected that 1734 infants will be included in the study.

With a total sample size of 1734 infants and an approximate prevalence for NH of 15%, the statistical power (two-sided 95% confidence interval) of a relative difference in the risk of NH of 1.5 fold and 2-fold, in association with a binary risk factor with a prevalence of 10, 20 or 50%, is presented (Table 1).

**Table 1 Tab1:** Statistical power calculations

	Relative risk (RR) for NH associated with binary risk factor	
	RR = 1.5	RR = 2.0
Binary risk factor prevalence	Statistical power	
10%	71%	99%
20%	86%	99%
50%	97%	99%

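### The primary outcome is a relative risk and a population-attributable fraction, but the only model named for it is logistic regression, and at a 15% risk odds ratios do not approximate relative risks

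*Protocol article*

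**What the plan says.** Three sections of the protocol article bear on this point.

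- **Outcomes.** The primary outcome is "to measure the relative risk of factors associated with moderate and severe NH in infants born at SMRU" and "to calculate their population-attributable fraction". Both quantities are functions of risks.
- **Sample size.** Power is given for RRs of 1.5 and 2.0, with 1734 infants, "an approximate prevalence for NH of 15" per cent and a "two-sided 95% confidence interval". Table 1 covers risk-factor prevalences of 10%, 20% and 50%.
- **Data collection and analysis.** For NH risk factors, "univariate and multivariate logistic regressions will be performed to identify risk factors for NH". Model building is also logistic: "Stepwise logistic regression modelling with backward elimination will be performed on the subset of candidate risk factors".

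The other models in the analysis section (linear regression for the neurocognitive score, modelling of serum bilirubin) serve secondary outcomes. The article names no risk-ratio model, no standardisation of the logistic results and no PAF estimator.

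**The concern.** The plan fixes its primary outcome on the risk scale and its primary model on the odds scale. The two nearly coincide when the outcome is rare, but 15% is not rare. The usual output of the named model is a table of adjusted ORs. If those are labelled as RRs, or inserted into a PAF formula, each factor looks stronger than it is, and a factor's apparent share of NH cases grows with it. The Background says that the results will inform the allocation of scarce resources, so the PAFs are meant to be used. The design does not force the OR scale, because a prospective cohort can estimate risks directly.

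**Working it through.** **Inputs.** From the Sample size section and Table 1: N = 1734, NH risk 15%, two-sided 5% level, RR 1.5 and 2.0, exposure prevalence e = 10%, 20%, 50%. The article does not say whether 15% is the risk overall or in unexposed infants. The main results below take it as the overall risk; the other reading is in step 4.

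**1. The plan's own figures.** 2040 × 0.85 = 1734, as stated. For Table 1, the pooled two-proportion power is

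Φ{ [ |p1 − p0| − 1.96·√(p̄(1−p̄)(1/n0 + 1/n1)) ] / √(p0(1−p0)/n0 + p1(1−p1)/n1) }, with n1 = e·N and n0 = (1−e)·N.

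| RR 1.5, exposure | Stated | 15% in unexposed | 15% overall | 1.5 read as an OR (15% in unexposed) |
|---|---|---|---|---|
| 10% | 71% | 70.6% | 68.3% | 53.0% |
| 20% | 86% | 90.1% | 86.7% | 74.8% |
| 50% | 97% | 98.0% | 93.9% | 89.6% |

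For RR 2.0 all cells compute to about 99% or more under either reading of the 15%. No single variant that was tried returns every cell: the 20% cell fits one reading, and the 10% and 50% cells fit the other better. That is a separate minor matter. What counts here is that reading 1.5 as an OR falls far short of the stated power, so Table 1 is on the RR scale, as its heading says.

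**2. OR implied by each RR (15% overall).** p0 = 0.15 / (1 + e(RR − 1)); p1 = RR·p0; OR = [p1/(1 − p1)] / [p0/(1 − p0)].

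Example, e = 0.10 and RR 2.0: p0 = 0.15/1.1 = 0.1364; p1 = 0.2727; OR = (0.2727/0.7273)/(0.1364/0.8636) = 2.375.

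**3. PAF with the RR and with the OR in its place.** Levin: e(RR − 1)/[1 + e(RR − 1)]. Miettinen: pc(RR − 1)/RR, where pc = e·p1/0.15 is the exposed share of cases. With the true RR the two agree.

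Same example: true PAF = 0.1/1.1 = 9.1%. Levin with the OR: 0.1375/1.1375 = 12.1%. Miettinen with the OR: pc = 0.02727/0.15 = 0.1818, and 0.1818 × 1.375/2.375 = 10.5%.

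| e | RR | OR | OR/RR | True PAF | Levin with OR | Miettinen with OR |
|---|---|---|---|---|---|---|
| 10% | 1.5 | 1.64 | 1.09 | 4.8% | 6.0% | 5.6% |
| 20% | 1.5 | 1.63 | 1.09 | 9.1% | 11.2% | 10.5% |
| 50% | 1.5 | 1.61 | 1.07 | 20.0% | 23.4% | 22.7% |
| 10% | 2.0 | 2.38 | 1.19 | 9.1% | 12.1% | 10.5% |
| 20% | 2.0 | 2.33 | 1.17 | 16.7% | 21.1% | 19.0% |
| 50% | 2.0 | 2.25 | 1.13 | 33.3% | 38.5% | 37.0% |

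**4. Sensitivity.**
- 15% in the unexposed: RR 1.5 gives OR 1.65 and RR 2.0 gives OR 2.43.
- Protective factor, 15% in the unexposed: RR 0.5 gives OR 0.46. The exaggeration is away from 1, not always upward.
- Severe NH alone: the article gives no risk. On an assumed 1% to 5% in the unexposed, RR 2.0 gives OR 2 × 0.99/0.98 = 2.02 to 2 × 0.95/0.90 = 2.11.

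**5. Ordering of factors.** Under Levin's formula with the OR, no pair of the six scenarios reverses, but the tie at 9.1% splits into 11.2% and 12.1%, so nearly tied factors could swap. Under Miettinen's formula with an unadjusted OR, the result reduces to the true PAF divided by (1 − p0). At a fixed overall risk it depends on p0 alone, so the order is kept and the tie stays a tie (10.5% for both).

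**6. Can the planned model deliver the outcome?** Yes. For e = 20% and RR 2.0 the logistic fit predicts risks of 0.25 and 0.125. Standardising gives RR = 0.25/0.125 = 2.0 and PAF = (0.15 − 0.125)/0.15 = 16.7%, the true values.

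**The case against.** The best defence is that nothing in the article says ORs will be presented as RRs. The analysis section gives logistic regression the task of identifying factors, by univariate screening and backward elimination, and that is a legitimate use. The same fitted model yields valid RRs and PAFs by standardisation (step 6). The text is also a condensed article, and a full protocol or analysis plan may set out that last step, the PAF estimator and its interval.

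Much of this stands. Any bias is conditional on how the ORs are used, and the absence of an estimator's details from an article would be no finding by itself. What remains is a mismatch between two things the article does state: an outcome and a power table on the risk scale, and a sole named model that reports on the odds scale at a risk where the scales differ.

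Two stronger readings are tempting. A reader might infer that the plan's ORs will overstate the primary results; the documents support this only if ORs are substituted for RRs. A reader might also infer that the ranking of factors, and so the resource advice, would be wrong. Step 5 does not support that: the order can change among close factors under one formula and is kept under the other.

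**Conclusion.** The point holds as an inconsistency between the stated primary outcome and the stated model. In the Table 1 scenarios, with 15% as the overall NH risk, ORs exceed RRs by 7% to 9% at RR 1.5 and by 13% to 19% at RR 2.0. PAFs computed with an OR in place of the RR would be about 11% to 33% too high in relative terms, depending on formula and exposure. These sizes rest on the article's approximate 15% for NH as a whole and on unadjusted, single-factor arithmetic. The distortion would be small for severe NH alone if that is rare, which is an assumption. Factor selection by hypothesis test is not invalidated. The mismatch is moderate, but it concerns the primary outcome and should be settled before the analysis is run.

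**What to change.** In Data collection and analysis, state that the primary results are:

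- adjusted RRs, from modified Poisson regression with robust variance or from marginal standardisation of the logistic model already planned;
- adjusted PAFs, by standardisation in infants born at SMRU, with bootstrap confidence intervals;
- ORs as supplementary results only.

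Name the SMRU-born set explicitly. The Outcomes section restricts the primary outcome to it, but the analysis section excludes outside births only from the incidence calculation, and infants born elsewhere who present after 48 hours are eligible only if jaundiced.

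The cost is a few sentences of analysis wording and some programming. No new data are needed and the sample size does not change. If the full protocol or analysis plan already specifies these steps, a reference to it would be enough.

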## Discussion

There are several strengths to the proposed protocol. First, it is a prospective birth cohort study. The active screening for NH will help early detection, treatment and severity categorization of the NH. Moreover, it will allow the comparison of neurodevelopmental scores at 1 year of age between infants with and without NH, an important and unique feature of the study.

Secondly, the collection of umbilical cord blood will provide valuable information otherwise rarely available on possible NH predisposing factors, such as the presence of a UGT1A1 polymorphisms (Gly71Arg and TATA promotor) associated with or without Gilbert’s and/or Crigler-Najjar syndrome [16], or Southeast Asian Ovalocytosis [17, 18].

G6PD-testing (fluorescent spot test) performed on the cord blood can be falsely normal because of the high number of reticulocytes and young red blood cells with a higher level of activity or when haemolysis is present [19]. For this reason the fluorescent spot test will be repeated in all infants at the age of one month. This will give valuable information about the reliability of one of the most frequently used screening tests in resource-constrained settings where the test is most often performed only at birth.

G6PD-deficiency is very common among the refugee and migrant populations living on the Thai-Myanmar border [20]. This study will quantify the contribution of G6PD-deficiency to the incidence and severity of NH in these populations. It will confirm clinical experience that a high proportion (25%) of newborns requiring phototherapy are G6PD-deficiency and that these newborns require a longer phototherapy duration [21]. Furthermore it will account for a common practice in these populations [22]: the use of naphthalene creams or balls containing naphthalene stored with infant clothes. There is a risk for the infant of naphthalene skin absorption, inhalation or accidental ingestion, which is a known cause of haemolysis in G6PD deficient patients [23, 24].

As eligible babies are from mothers who followed ANC and the majority of mothers give birth in SMRU facilities, detailed pregnancy information will be available. In Asia, ABO blood group incompatibility and G6PD-deficiency are the two most commonly known causes of NH [1].

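### The stated reason for studying naphthalene applies to G6PD-deficient infants, but the risk-factor analysis screens it as an all-infant effect at univariate p < 0.10, which dilutes an effect concentrated in those infants

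*Protocol article*

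**What the plan says.** All places are in the protocol article.

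- **Discussion.** On naphthalene creams and balls: "Furthermore it will account for a common practice in these populations". The reason given is that naphthalene reaches the infant through skin, inhalation or ingestion, "which is a known cause of haemolysis in G6PD deficient patients".
- **Study procedures.** Mothers are asked about naphthalene. G6PD is tested on cord blood and again at one month. The Discussion explains the repeat: the cord-blood result can be falsely normal.
- **Data collection and analysis.** A causal diagram will be drawn. Univariate and multivariate logistic regressions follow, with backward elimination "performed on the subset of candidate risk factors selected based on *p*-value < 0.10 in the univariate regression analyses". Only key confounders from the diagram are exempt from the screen; naphthalene is not named among them. On subgroups: "Pre-planned subgroup analysis will be conducted in order to identify risk factors associated with moderate and severe NH", with a second purpose concerning neurodevelopment. No product term and no analysis by G6PD status is mentioned.
- **Outcomes.** The primary outcome is the relative risk of each factor and its population-attributable fraction.
- **Sample size.** Table 1 gives power for a single binary factor acting on all infants.

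**The concern.** The mechanism that the protocol cites operates in a minority of infants, while the selection rule looks at the average effect over everyone. If the effect is confined or nearly confined to deficient infants, that average is small, and naphthalene may be removed before the multivariable model is built. If it survives, the relative risk and attributable fraction are averages over two groups with different effects, and deficient infants get no estimate of their own.

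This is not the usual criticism of stepwise selection: a fully adjusted main-effects model with no selection would show the same dilution. Naphthalene is an avoidable exposure that the protocol singles out, and the results are meant to feed local guidance. A dropped or diluted result could be read as reassurance for the infants in whom harm is suspected.

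**Working it through.** **The plan's own figures.** From "2040 infants born alive of 28 weeks or more gestational age" and "15% of infants will be lost to follow-up before completion of the study": 2040 × 0.85 = 1734, which agrees with "It is expected that 1734 infants will be included in the study". Table 1 is reproduced only in part. Taking 15% as the risk in the unexposed, a pooled-variance two-proportion test gives 70.6 / 90.1 / 98.0% for RR 1.5 (stated 71 / 86 / 97%) and 99.5 / 100 / 100% for RR 2.0 (stated 99% throughout). Nothing below depends on this mismatch.

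**Inputs from the protocol.** N = 1734; NH 15%; screen at p < 0.10 (taken as two-sided); 25% of newborns needing phototherapy are G6PD-deficient, used here as a proxy for the deficient share *s* of NH cases.

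**Assumptions not in the protocol.** RR 2.0 in deficient and 1.0 in normal infants; exposure *f* of 10-50%, unrelated to G6PD status; G6PD deficiency 10% or 15%.

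**Dilution.** Let c = 0.15s/(1 + f). The all-infant risks are

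- unexposed: p0 = 0.15(1 − s) + c
- exposed: p1 = 0.15(1 − s) + 2c

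G6PD prevalence cancels. For f = 20%, s = 25%: c = 0.0375/1.2 = 0.03125, p0 = 0.14375, p1 = 0.1750, pooled RR = 1.217.

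**Passing the screen, f = 20%.** There are 347 exposed and 1387 unexposed infants.

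- Null SE = √[0.15 × 0.85 × (1/347 + 1/1387)] = 0.0214
- Alternative SE = √[0.175 × 0.825/347 + 0.14375 × 0.85625/1387] = 0.0225
- Power = Φ[(0.03125 − 1.645 × 0.0214)/0.0225] = Φ(−0.18) = 43%

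**Within deficient infants.** At 10% deficiency there are about 173 infants with mean risk 0.0375/0.10 = 0.375; at f = 20% this splits into 0.3125 and 0.625. At 15% deficiency there are about 260, with mean risk 0.25, splitting into 0.208 and 0.417. Power comes from 20,000 simulated cohorts per setting, with Wald tests on the log odds ratio.

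| Exposure | Pooled RR | Screen, p < 0.10 | Deficient infants only, 0.05 | Product term, 0.05 |
|---|---|---|---|---|
| 10% | 1.23 | about 35% | 69-77% | 55-67% |
| 20-50% | 1.22-1.18 | 42-46% | about 85-95% | 74-90% |

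**Attributable fraction, f = 20%.** Pooled: 1 − 0.14375/0.15 = 4.2%. In deficient infants: 1 − 1/1.2 = 16.7%. In normal infants: 0. The pooled value is the correct average (0.25 × 16.7% = 4.2%), but it hides the group concerned.

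**Sensitivity of the screen's pass rate (exposure 20-50%, one change at a time).**

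| Change | Pass rate |
|---|---|
| Deficient share 20% | 32-35% |
| Deficient share 30% | 54-58% |
| N = 2040 | 47-52% |
| RR 1.1 in normal infants | 62-69% |
| RR 2.5 in deficient infants | 59-66% |

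At RR 1.5 in deficient infants (exposure 10-50%), both tests are weak: about 18-24% for the screen against 28-54% within deficient infants.

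**The case against.** A reader might infer that the plan fails to test a hypothesis it has stated, and that the screen would miss a doubling of risk more often than not. The document supports neither.

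- **No hypothesis is stated.** The protocol promises to take naphthalene use into account and gives a mechanism. It does not say that there is no effect in G6PD-normal infants, and it promises no estimate in deficient ones. The RR 2.0/1.0 scenario is an assumption of this check.
- **A pass rate below one half is not robust.** It fails at a 30% deficient share, at RR 2.5, or with RR 1.1 in infants classed as normal. The last is plausible, since cord-blood tests can be falsely normal and heterozygous females may be affected. It is about even at N = 2040, which is arguable because the 15% loss is counted to study completion whereas bilirubin is measured in the first week.
- **Naphthalene might escape the screen.** The causal diagram is not shown and could force it in. This stands, but its estimate would still be an all-infant one.
- **A condensed article may leave interaction terms to a fuller plan.** That is fair for the product term itself. The screening rule, however, is fixed here, and followed as written it can remove naphthalene before any such term is considered.
- **The alternative looks better than it would in practice.** Its power assumes error-free G6PD classification, falls at 10% exposure, and is modest at RR 1.5.

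What remains is the dilution. With no effect in normal infants, the 0.05 test within deficient infants had more power than the looser screen in every setting run.

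**Conclusion.** The point holds as a mismatch between the reason given for studying naphthalene and the way the analysis would look at it. Under RR 2.0 in deficient and 1.0 in normal infants, N = 1734, 15% NH and a 25% deficient share, the all-infant relative risk is about 1.2. At 20-50% exposure the screen's 42-46% pass rate is some 40 to 50 percentage points below the power within deficient infants. The gap, not the exact pass rate, is the finding: the pass rate moves from about one third to over two thirds with the deficient share, the effect sizes and N. Exposure prevalence and G6PD prevalence are assumed; the second affects only the deficient-infant and product-term figures. No stated figure is wrong on this account. It is a worthwhile, inexpensive change to the analysis of one exposure.

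**What to change.** Add one sentence to Data collection and analysis: naphthalene exposure, G6PD status and their product term stay in the NH model regardless of univariate p-value, and the naphthalene relative risk and attributable fraction are reported with 95% confidence intervals separately for G6PD-deficient and G6PD-normal infants. Classify G6PD status by the one-month repeat where available, since the cord-blood test can be falsely normal.

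No new data are needed. The cost is one extra pre-specified term and a wide interval in deficient infants: about 173 to 260 infants at 10-15% deficiency, of whom only 17 to 26 would be exposed at 10% exposure. That interval would also show plainly how much the study can say about this group.

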## Discussion

There are several strengths to the proposed protocol. First, it is a prospective birth cohort study. The active screening for NH will help early detection, treatment and severity categorization of the NH. Moreover, it will allow the comparison of neurodevelopmental scores at 1 year of age between infants with and without NH, an important and unique feature of the study.

Secondly, the collection of umbilical cord blood will provide valuable information otherwise rarely available on possible NH predisposing factors, such as the presence of a UGT1A1 polymorphisms (Gly71Arg and TATA promotor) associated with or without Gilbert’s and/or Crigler-Najjar syndrome [16], or Southeast Asian Ovalocytosis [17, 18].

G6PD-testing (fluorescent spot test) performed on the cord blood can be falsely normal because of the high number of reticulocytes and young red blood cells with a higher level of activity or when haemolysis is present [19]. For this reason the fluorescent spot test will be repeated in all infants at the age of one month. This will give valuable information about the reliability of one of the most frequently used screening tests in resource-constrained settings where the test is most often performed only at birth.

G6PD-deficiency is very common among the refugee and migrant populations living on the Thai-Myanmar border [20]. This study will quantify the contribution of G6PD-deficiency to the incidence and severity of NH in these populations. It will confirm clinical experience that a high proportion (25%) of newborns requiring phototherapy are G6PD-deficiency and that these newborns require a longer phototherapy duration [21]. Furthermore it will account for a common practice in these populations [22]: the use of naphthalene creams or balls containing naphthalene stored with infant clothes. There is a risk for the infant of naphthalene skin absorption, inhalation or accidental ingestion, which is a known cause of haemolysis in G6PD deficient patients [23, 24].

As eligible babies are from mothers who followed ANC and the majority of mothers give birth in SMRU facilities, detailed pregnancy information will be available. In Asia, ABO blood group incompatibility and G6PD-deficiency are the two most commonly known causes of NH [1].

On the negative side, women who choose not to attend ANC or are unable to attend will be omitted from this study. These women are known to be at higher risk of complications in labour and their offspring might need more medical attention [25]. Nonetheless there is a possibility for infants born outside the SMRU birth units and presenting within 48 h of life (or up to 8 days of life in infants with NH) to be included in the study and to be followed up until one year of age.

This protocol has some additional identifiable limitations. First, inclusion of infants is limited to those born after the gestational age of 28 weeks thus potentially reducing the overall incidence of NH. Severely preterm infants are at risk of severe NH and neurological impairment due to NH but survival in resource constrained settings before 28 weeks is extremely rare as ventilator assistance is unavailable. Infants who are born before 28 weeks are given supportive care and excluded from this analysis, as described and recommended by Turner et al. [21]. The estimation of gestation with ultrasound before 14 weeks of pregnancy is reliable and the quality of ultrasound service in the SMRU clinics is high [26]. If the mother attends ANC after the 24 weeks of gestational age the next best estimate will be chosen from the Dubowitz test [27] or last menstrual period if known.

A second limitation of this study is that the follow-up will last only one year and no auditory tests or magnetic resonance imaging are available. It means that the diagnosis of kernicterus will not be explored in as much detail as is possible in resource rich settings [28]. Kernicterus is most usually characterized by choreoathetoid cerebral palsy, impaired upward gaze, and sensorineural hearing loss whereas cognition is relatively spared [28]. There is also controversial discussion about the relationship between NH and developmental delay, cognitive impairment or behavioural disorders [29]. These will only become evident when the child is older than one year of age. Strict definitions of moderate and severe NH and treatment protocols will help minimize these limitations [6].

Interpretation of the data must consider the use of different types of phototherapy in the SMRU clinics (bulbs and Light-emitting diode units). Differences in irradiance will be recorded to help reduce bias in the interpretation of the results. The Bilirubin Induced Neurological Dysfunction (BIND) Score [30] has recently been validated for resource-limited settings in Africa. Unfortunately, the BIND score was not included in this study protocol. However medical staff working in the SCBU have learned to systematically describe in their ‘daily observation sheet’ the neonate’s tone, alertness, movements and sucking behaviour. This should be enough to reconstitute the BIND score, at least partially, to evaluate and categorize the neurological evolution of the neonate during their hospitalization in the SCBU.

